|-----------------------------|----------------------------------------|------------------------------------------------------------------------------------------------------------------------------------------------------------------------------------------------------------------------------------------------------------------------------------------------------------------------------------------------------------------------------------------------------------------------------------------------------------------------------------------------------------------------------------------------------------------------------------------------------------------------------------------------------------------------------------------------------------------------------------------------------------------------------------------------------------------------------------------------------------------------------------------------------|-------------------------------------------|----------------------|
|                             | NZ pharmaceuticals collection          | 
High blood pressure
 
Angiotensin converting enzyme (ACE) inhibitors
 
(i.e. Captopril, Cilazapril, Enalapril, Lisinopril, Perindopril, quinapril)
 
Angiotensin receptor blockers (ARBs) (i.e. Candesarten, Losarten, Irbesarten)
 
Beta blockers (Atenolol, bisoprolol, carvedilol, celiprolol, labetalol, metoprolol, propranolol, sotalol)
 
Diuretics (hydrochlorothiazide, bendroflumethiazide, chlorthalidone, indapamide)
 
Calcium channel blockers (amlodipine, diltiazem, felodipine, nifedipine)
 
Combination (inhibace plus, accuretic, Arrow-Losartan & Hydrochlorothiazide)
 
Dyslipidaemia
 
Statins (Atorvastatin, Pravastatin, Rosuvastatin, Simvastatin)
 
Fibrate (bezafibrate)
 
Niacin derivatives (acipimox)
 
Ezetimibe
 |                                           |                      |

| Study Outcome (definitions)                                                                                                                                                                                                                                                                                                                                                                                     | Priority Order for use of Data Sources | Details of data*:                                                                                                                                                                                                              | Criteria for adjudication (if applicable)                                                                                                                                                                                                                                                                                                                                                               | Comments/ Reference: |
|-----------------------------------------------------------------------------------------------------------------------------------------------------------------------------------------------------------------------------------------------------------------------------------------------------------------------------------------------------------------------------------------------------------------|----------------------------------------|--------------------------------------------------------------------------------------------------------------------------------------------------------------------------------------------------------------------------------|---------------------------------------------------------------------------------------------------------------------------------------------------------------------------------------------------------------------------------------------------------------------------------------------------------------------------------------------------------------------------------------------------------|----------------------|

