### Sensitivity analyses

The following sensitivity analyses will be performed:

- Excluding participants with asthma diagnosed <5 and no current asthma (subgroup of primary outcome).
- Excluding participants with respiratory outcomes derived from hospital admission data where the respiratory diagnosis was not the primary reason for admission (subgroup of composite outcome).

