| Primary outcome                                                                                                                                                                                                                                                                                                                                                      |                                        |                                                                                                                                                                                                                                                                                                                                                                                                             |                                                                                                                    |                                                                                                                                                                                                                     |
| Any asthma diagnosis
Defined as the presence of either of: 
 
Self-report of a doctor's diagnosis of asthma.
 
Hospital admissions with diagnostic codes for asthma at any age.
 
Dispensing of pharmaceuticals for asthma at any age at least one repeat prescription more than 1 day apart.
 
 | Self-report questionnaire              | B22. Have you ever been told by a doctor that you have asthma?                                                                                                                                                                                                                                                                                                                                              | If answers no to question about asthma but has evidence from only one other data source, then will be adjudicated. |                                                                                                                                                                                                                     |

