|                                                                                                                                                                                                                                                                                                                                                                      | NMDS admissions data                   | Admissions with the following ICD-10AM codes:
J45.0 – J45.998 Asthma and subcodes.
J46 status asthmaticus
R06.2 Wheezing
U833 Asthma, without mention of chronic obstructive pulmonary disease                                                                                                                                                                                                  |                                                                                                                    | https://www.hqsc.govt.nz/assets/Our-data/Publications-resources/Methodology-asthma-update-2020.pdf |
|                                                                                                                                                                                                                                                                                                                                                                      | NZ pharmaceuticals collection          | Prescriptions + dates
Short acting beta agonist (SABA):
Salbutamol ( Ventolin, respigen, SalAir ), terbutaline ( Bricanyl ).
Long acting beta agonists (LABA):
Eformoterol fumarate ( Oxis, Foradil ), salmeterol ( Serevent, Meterol ),
Inhaled corticosteroid (ICS):
Beclometasone dipropionate ( Beclazone, Qvar ), budesonide |                                                                                                                    | https://www.hqsc.govt.nz/assets/Our-data/Publications-resources/Methodology-asthma-update-2020.pdf |

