| 
Asthma currently on treatment
 
Defined as the presence of either of:
 
 
1. Self-report of a doctor's diagnosis of asthma AND currently on treatment.
 
2. Hospital admissions with diagnostic codes for asthma at any age.
 
3. Dispensing of pharmaceuticals for asthma for at least one repeat prescription more
 
 | Self-report questionnaire              | 
B22. Have you ever been told by a doctor that you have asthma?
 
B23. What treatments do you now have for asthma?
                                                                                                                                                                                                                                                                                                                                                                                                   | If answers no to question about asthma but has evidence from one other data source then will be adjudicated. | 
Timeframe of last 2 years to account for those with seasonal asthma who may only have received their last script last season.
 
Administrative data will be right censored at the date of the questionnaire for participants who completed the questionnaire and at the date of consent for those who did not.
 |

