| than 1 day apart and within last 2 years. |                                        |                                                                                                                                                                                                                                                                                                                                                                                                                                                                                                                                                                                                                                                                                                                                                                                                                     |                                           |                                                                                                                                                                                                                     |
|                                           | NMDS admissions data                   | Admissions with the following ICD-10AM codes:
J45.0 – J45.998 Asthma and subcodes.
J46 status asthmaticus
R06.2 Wheezing                                                                                                                                                                                                                                                                                                                                                                                                                                                                                                                                                                                                                                                                                   |                                           | https://www.hqsc.govt.nz/assets/Our-data/Publications-resources/Methodology-asthma-update-2020.pdf |

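### One identically worded admission criterion has two code lists: U833, labelled asthma, is listed for any asthma diagnosis but not for asthma currently on treatment, and no reason is given

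*SAP*

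**What the plan says.** Appendix 15.2 defines each asthma outcome by three alternative criteria: self-report, hospital admission and dispensing. The admission criterion is the same sentence in the rows for any asthma diagnosis and asthma currently on treatment: "Hospital admissions with diagnostic codes for asthma at any age". Both NMDS entries open with "J45.0 – J45.998 Asthma and subcodes", continue with J46 and R06.2, and cite the same external methodology document. The primary entry then adds "U833 Asthma, without mention of chronic obstructive pulmonary disease". The secondary entry stops at "R06.2 Wheezing".

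The rows also carry adjudication rules for a participant who says no to the asthma question. For the primary outcome the case is adjudicated if the participant "has evidence from only one other data source, then will be adjudicated". For the secondary outcome the wording is "has evidence from one other data source then will be adjudicated".

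Section 13 has a sensitivity analysis of the primary outcome described as "Excluding participants with asthma diagnosed <5 and no current asthma". It does not say which definition of current asthma applies.

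**The concern.** A criterion that asks for asthma diagnostic codes should lead to the same set of codes wherever it appears. Here a code whose own label is asthma belongs to the set for the primary outcome and is absent from the set for the first-listed secondary outcome. A programmer who works from the criterion and one who works from the printed list could derive different secondary variables. Nothing in the SAP says which of them would be right.

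At stake is the classification of participants whose only asthma admission code is U833. If the sensitivity analysis in Section 13 takes current asthma from the secondary row, the same difference could also decide who is removed there.

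**Working it through.** No power, alpha or event figure is involved, so the check is a comparison of the two lists followed by a trace of who is affected.

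**1. The two lists**

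| Code | Any asthma diagnosis | Asthma currently on treatment |
|---|---|---|
| J45.0 to J45.998 | listed | listed |
| J46 | listed | listed |
| R06.2 | listed | listed |
| U833 | listed | absent |

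The primary list minus the secondary list is {U833}. The secondary list minus the primary list is empty.

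**2. Is the gap explained, or an artefact?**

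- The secondary entry looks complete. It ends at R06.2 and the pharmaceutical source follows directly, so text lost in PDF extraction is unlikely.
- The SAP has no general rule against U-codes. Appendix 15.2 accepts U804, U794 and U803 for neurodevelopmental disability, U822 for cardiovascular outcomes, U781 for obesity, U793 for depression and U864 for bone disease.
- The pharmaceutical lists in the two asthma rows are the same. Only the admission lists differ.
- A wish to capture recent disease does not account for it. The 2-year window is written into the dispensing criterion, while the admission criterion keeps its any-age wording.
- Neither addendum mentions U833.

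**3. Who is treated differently?** Take a participant whose only asthma admission code is U833.

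*Primary outcome (U833 listed)*
- Yes to B22: already a case by self-report, so U833 adds nothing.
- No to B22, with U833 the only other evidence: adjudicated, not counted automatically.
- B22 unanswered: the admission criterion is met through U833.

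*Secondary outcome (U833 absent)*
- Reports an asthma diagnosis and current treatment: the self-report criterion is met with or without U833.
- Repeat dispensing within the last 2 years: the dispensing criterion is met with or without U833.
- Neither of these: no criterion is met as written. With U833 listed, the admission criterion would be met, subject to adjudication if the participant answered no.

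The omission therefore decides whether any secondary criterion is met only in that last case.

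**4. Size per participant**

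Input: 214 consenting participants (Section 10, Analysis approach). The text gives no arm sizes, so equal arms are assumed: 214 / 2 = 107. One reclassified participant is 1 / 107 = 0.9 percentage points of one arm, or 1 / 214 = 0.5 percentage points of the whole sample. The SAP gives no counts by code, so the number of such participants cannot be derived.

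**The case against.** The strongest defence is that the outcomes have different purposes, and a narrower list for current asthma may be deliberate. Adding U833 could also turn someone who reports past asthma but no current treatment into a case of asthma currently on treatment. The methodology document cited in both rows is not available here, so which list follows it cannot be checked. Part of this stands: intent cannot be settled from the SAP, and a stated reason for leaving U833 out would be an acceptable answer. It does not remove the inconsistency, because the secondary criterion still asks for asthma codes at any age, and an old J45 admission already produces the same kind of case. Whether any-age admissions suit a current outcome is a separate question.

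Four stronger readings are tempting and are not supported:

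- A reader might infer that hospital-recorded asthma in general counts for one outcome and not the other. It does not. J45 and J46 admissions count for both.
- A reader might treat the wheeze code as part of the discrepancy. R06.2 is in both lists. Whether a symptom code belongs under asthma is a different matter.
- A reader might suppose that a U833 admission alone always makes a primary case. After a no to B22 with no other evidence, it leads to adjudication.
- A reader might conclude that the sensitivity analysis is affected. Section 13 does not refer to the secondary row, so this is only a possibility.

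**Conclusion.** The inconsistency is real and can be checked line by line: one criterion, two lists, one code of difference, no reason given. It is minor. It concerns only asthma recorded solely as U833. For the secondary outcome it also requires that the participant reports no current treatment and has no repeat dispensing in the last 2 years.

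The number affected is unknown and may be zero. The figure of 0.9 percentage points is per person and rests on the assumption of equal arms; it is not an estimate of bias. The stated sample size and power do not depend on this point. That the omission was an oversight is the more natural reading, given the shared wording and the U-codes accepted elsewhere, but the SAP does not establish it.

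**What to change.** By dated addendum, use one asthma admission code list, including U833, for both outcomes, under whatever time limit applies to the current outcome. If U833 was left out of the second list on purpose, state the reason instead. If current asthma in the Section 13 sensitivity analysis is meant to come from this row, say so and point it to the same list.

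Then rederive asthma currently on treatment, refit its adjusted and unadjusted models and its subgroup models for sex and deprivation, and report whether any participant changes category. If none does, one sentence to that effect closes the matter.

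The cost is small but is more than a line of wording. The addendum that added tertiary outcomes records that all analyses had already been completed, before unblinding of treatment groups, so the change means refitting existing models and should be dated relative to unblinding. There is a precedent: the other addendum removed a stroke item from the cardiovascular composite to bring its detailed definition into line with the outcome lists.

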### Study hypothesis

Repeat antenatal corticosteroids reduce neonatal mortality and morbidity without long-term adverse impacts on health and social outcomes in offspring (F1).

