## 3. Background: The Australasian Collaborative Trial of Repeat Doses of Steroids (ACTORDS)

### ACTORDS RCT

In this multicentre centre, two-arm, parallel, randomised double blind placebo-controlled trial, women who remained at risk of preterm birth at less than 32 weeks' gestation, 7 or more days after receiving a first course of prenatal corticosteroids, were randomly assigned to receive a repeat intramuscular dose of either betamethasone or saline placebo. This could be repeated every week the woman remained undelivered, at less than 32 weeks' gestation, if still considered to be at risk of preterm birth in the next 7 days. Primary outcomes were occurrence and severity of neonatal respiratory distress syndrome, severity of any lung disease present, use and duration of oxygen and mechanical ventilation, and weight, length, and head circumference at birth and hospital discharge.

The RCT found that fewer babies exposed to repeat corticosteroids had respiratory distress syndrome and fewer had severe lung disease than those in the placebo group. In keeping with these benefits, babies exposed to repeat corticosteroids needed less oxygen therapy, and shorter duration of mechanical ventilation. Mean weight, length, and head circumference at birth and hospital discharge did not differ between treatment groups. Z-scores for weight and head circumference at birth were lower in the babies who received repeat corticosteroids although at the time of hospital discharge Z-scores did not differ between treatment groups.

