## 5. Study outcomes

Outcome definitions and the hierarchical approach to different data sources are listed below and detailed in the [appendix](#). All components of the composite secondary outcomes will be reported separately as tertiary outcomes. Administrative data will be right censored at the date of the questionnaire for participants who completed the questionnaire and at the date of consent for those who did not.

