### Secondary Outcomes:

- Asthma currently on treatment
- Death (any cause after randomisation)
- Respiratory outcomes (composite) – any respiratory diagnoses other than asthma including chronic lung disease
- Neurodevelopmental disability (composite) – any of:
  - visual impairment
  - hearing impairment
  - intellectual impairment
  - cerebral palsy
  - epilepsy
  - autism spectrum disorder (including Asperger's syndrome)
  - attention deficit disorder (ADD) or attention deficit hyperactivity disorder (ADHD)
- Cardiovascular outcomes (composite) – any cardiovascular diagnosis including hypertension, cardiomyopathies, arrhythmias, heart failure but excluding congenital heart disease
- Number of cardiovascular disease risk factors (composite categorised as 0, 1 or >1 risk factors) – any of:
  - high blood pressure
  - dyslipidaemia

- diabetes mellitus
- obesity/overweight
- Diabetes outcomes (composite) – any of prediabetes, diabetes mellitus, gestational diabetes mellitus
- Mental health outcomes (composite) – any mental health diagnosis including depression, bipolar affective disorder, schizophrenia, anxiety disorders, suicide/self-harm
- Bone health outcomes: any diagnoses related to bone disease
- Bone health outcomes: number of fractures
- General health outcomes: self-reported general health (reported health fair or poor)
- General health outcomes: functional difficulties (categorised as no disability / moderate or non-severe disabilities / severe disabilities)
- General health outcomes: oral health (reported oral health fair or poor or tooth extractions)

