|                                                                                                                                                                                                                                                                       |                                        | Oral Treatments
Montelukast ( Montelukast Mylan, Apo-Montelukast, Montelukast Accord )                                                                                                                                        |                                           |                      |
| Death (any cause after randomisation)                                                                                                                                                                                                                          | MORT data                              | Death from any cause obtained from MORT dataset                                                                                                                                                                                                |                                           |                      |
|                                                                                                                                                                                                                                                                       | Trial follow up records                | Death from any cause as recorded in databases for original trial data and earlier follow-up studies.                                                                                                                                           |                                           |                      |
| Respiratory outcomes (composite)
Defined as the presence of either of: 
 
Self-report of a respiratory condition.
 
Hospital admissions with diagnostic codes for a respiratory condition at any age.
 
 | Self-report questionnaire              | Free text response indicating a respiratory condition to one of the following questions:
B41. Do you currently have any other major illnesses?
B42. Have you ever had any other major illnesses in the past?                             |                                           |                      |

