|                                                                                                                                                                                                                                                                                                                                                                                                       |                                        | P271 Bronchopulmonary dysplasia originating in the perinatal period
P278 Other chronic respiratory diseases originating in the perinatal period
P279 Unspecified chronic respiratory disease originating in the perinatal period
Q336 Hypoplasia and dysplasia of lung
S270 Traumatic pneumothorax
S2731 Contusion and haematoma of lung
S2732 Laceration of lung                                                                                                                                                            |                                           |                                                                                                                                                                                                                                                                                                                                                                                                                                                                                                                                        |

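### The respiratory composite counts hospital codes at any age with no start date, so neonatal lung disease and later respiratory disease are mixed and never separated by age

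*SAP*

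**What the plan says.** Section 5 of the SAP describes this secondary outcome as "any respiratory diagnoses other than asthma including chronic lung disease". Its row in the Appendix 15.2 definitions table gives two ways to be a case: a self-reported respiratory condition (free text at B41 or B42), or "Hospital admissions with diagnostic codes for a respiratory condition at any age". The admissions code list includes "P271 Bronchopulmonary dysplasia originating in the perinatal period", "P278 Other chronic respiratory diseases originating in the perinatal period" and the unspecified counterpart P279. It also has general codes such as J939, J969, J981, J982 and J984. It contains no code for respiratory distress syndrome.

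The only time rule for these data is in Section 5 and the footnote to the table: "Administrative data will be right censored at the date of the questionnaire", or at the consent date for participants without a questionnaire. No start date is given, and nothing is said about the birth admission.

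On the original trial, Section 3 reports that "fewer babies exposed to repeat corticosteroids had respiratory distress syndrome and fewer had severe lung disease than those in the placebo group". In Section 2 the aim concerns long-term impacts, and the hypothesis states neonatal benefit and the absence of long-term harm as two propositions. The one sensitivity analysis on this composite (Section 13) is "Excluding participants with respiratory outcomes derived from hospital admission data where the respiratory diagnosis was not the primary reason for admission". The components listed in Appendix 15.2 are infections, chronic conditions other than asthma, respiratory failure and trauma.

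**The concern.** With an end date but no start date, the window reaches back to birth. A child whose only listed code was recorded before first discharge home counts the same as one with bronchiectasis in adolescence. The mothers were at risk of preterm birth before 32 weeks, so the perinatal codes are relevant to this cohort.

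Neonatal lung disease is also where the original trial found an effect of treatment. If birth-admission codes are less frequent after repeat treatment, they pull the composite RR down whatever happens later. A later increase would then be understated, and with no later effect at all the composite could suggest a long-term benefit. Even if the birth-admission codes are balanced between arms, they add cases that carry no information on later disease and dilute a later effect.

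**Working it through.** **1. The text.** Three statements together decide the point: hospital codes count at any age, the only time limit is right censoring, and the list holds three codes that are perinatal by title. Nothing elsewhere in the SAP narrows this. The sensitivity analysis selects on whether the respiratory diagnosis was the primary reason for admission, so a birth-admission code can survive it. The components split by type of disease, so chronic conditions still pool neonatal and later diagnoses. Elsewhere the SAP does use time: death is counted from randomisation, and one asthma sensitivity analysis uses an age-5 cut.

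**2. The plan's own figure.** Section 8 gives 90% power with 214 participants for asthma, 35% v 57% (RR 0.57/0.35 = 1.63). With 107 per arm (equal split assumed) and two-sided 5%, the normal approximation gives 90.3%, so the figure reproduces. It concerns the primary outcome. The SAP gives no rate, effect or power for the respiratory composite.

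**3. Illustration.** Every rate here is an assumption.

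- Later disease: 20% placebo, 30% repeat (true later RR 1.5).
- Birth-admission codes: proportion q in placebo and q × r in repeat, where r is the neonatal RR.
- Birth-admission codes and later disease are independent.

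Composite risk, placebo = 1 − (1 − q)(1 − 0.20). Composite risk, repeat = 1 − (1 − q·r)(1 − 0.30).

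Example, q = 0.10 and r = 0.8: placebo 1 − 0.90 × 0.80 = 0.280; repeat 1 − 0.92 × 0.70 = 0.356; RR 1.27.

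Composite RR, with power at 107 per arm in brackets:

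| q in placebo | r = 1.0 | r = 0.8 | r = 0.67 | r = 0.5 |
|---|---|---|---|---|
| 10% | 1.32 (0.29) | 1.27 (0.22) | 1.24 (0.18) | 1.20 (0.14) |
| 20% | 1.22 (0.22) | 1.14 (0.12) | 1.09 (0.07) | 1.03 (0.04) |
| 30% | 1.16 (0.17) | 1.06 (0.06) | 1.00 (0.03) | 0.92 (0.07) |

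Counting later disease alone gives RR 1.50 and power 0.39.

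**4. Other later rates.** With 15% later disease in placebo and later RR 1.5, the same grid runs from 1.29 to 0.84. With 20% and later RR 1.75, it runs from 1.48 to 1.02.

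**5. No later effect (20% v 20%).** With q = 0.10 and r = 0.8: 1 − 0.92 × 0.80 = 0.264 against 0.280, RR 0.94. With 30% v 20% birth-admission codes: 1 − 0.80 × 0.80 = 0.36 against 0.44, RR 0.82. Either would be a neonatal difference showing in a 20-year outcome.

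**The case against.** A reader might infer that the known neonatal benefit will hide later harm. The documents do not support that. No respiratory distress syndrome code is listed, so that benefit is not counted directly. The SAP gives no treatment effect on chronic lung disease of perinatal origin. Full cancellation needs favourable assumptions: 30% v 20% at birth against 20% v 30% later gives 44% in both arms because the rates are mirror images. In the main grid, 10 of 12 cells stay above 1.00.

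A reader might also assume that the general J codes are usually recorded in the birth stay. The SAP does not say so; it only fails to bar them. That the admissions extract covers the birth stay is implied by the any-age wording, not stated.

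Nor does the point carry over to the cardiovascular composite. Its window is also open at the start, but the SAP reports no neonatal cardiovascular effect of treatment that could mask a later one.

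In the plan's favour, chronic lung disease is included deliberately, and a lifetime composite matches the any-age asthma outcome. Asthma is analysed separately, the components give some view of later infection, and the sensitivity analysis would drop cases whose lung code was secondary. Power for a later RR of 1.5 is low (0.39) even without the neonatal codes. These arguments limit the size and weigh against replacing the composite. They do not supply a separation by age.

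**Conclusion.** The point holds as a defect of definition in one secondary outcome: followed as written, the composite cannot distinguish neonatal lung disease from later respiratory disease, although the SAP's hypothesis does. The primary analysis is unaffected.

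The size cannot be determined from the SAP. Under the main assumptions a true later RR of 1.5 appears as about 1.32 to 0.92. Most of that range is dilution. Cancellation or reversal appears only with 30% birth-admission coding and a neonatal RR of 0.67 or lower; with later disease at 15%, reversal also appears at 20% coding and a neonatal RR of 0.5. These results rest on assumed rates, independence, an equal split of 214, and power calculations that ignore clustering and covariate adjustment. If children coded at birth are also more likely to have later disease, fewer are cases on birth codes alone and the mixing is smaller. The point should be corrected, but it does not invalidate the plan.

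**What to change.** Keep the any-age composite and make four additions to the SAP:

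- An analysis of the same composite in which the hospital limb is limited to admissions after first discharge home from the birth admission.
- Separate reporting, by arm, of respiratory codes from the birth admission, with a statement of whether the extract covers that stay.
- A rule for how P271, P278 and P279 are counted when recorded at a later admission.
- A statement that a difference in the any-age composite will not be interpreted as a long-term effect unless the post-discharge version agrees.

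This takes SAP text and a date filter on admissions data. The 31 July 2024 addendum says analyses were complete before unblinding. If the definition is already locked, the additions can be run and labelled under the post hoc provision in Section 13.

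The costs are fewer events and wider intervals in the post-discharge version. That version will also miss chronic lung disease managed without readmission, unless the participant reports it in the questionnaire. This is a reason to present it beside the any-age composite and not in its place.
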